### Preliminary enrollment and retention data

Enrollment and retention data for the first 7 months of recruitment are summarized in Fig. 3. At the time of publication, new enrollments were paused due to the Coronavirus (COVID-19) pandemic. Oregon Department of Corrections closed its facilites to non-essential staff and suspended all  visiting on March 13, 2020. Enrolled ROAR participants continued to receive follow up medical treatment and remote CRM services via secure video conference, phone, email, and text. Research check-ins, 3-month and 6-month follow-up surveys, and qualitative interviews continued by phone or secure videoconference.

**Fig. 3 Fig3:**
[figure not shown]
Preliminary ROAR enrollment: first 7 months of 18-month recruitment cycle (2/10/2020)

Early recruitment and retention rates suggest the that ROAR pilot will successfully enroll and retain participants as planned. Of 150 adults in custody referred for prescreening interview by end of month 7, 93% were screened using an in-person interview guide. Table 3 summarizes reasons why 32 women in custody were excluded from pre-screening interview process. Of those who completed the pre-screen interview (n=140), 61 were eligible to enroll. At total of 51participants (84% of those eligible at pre-screen) were consented and enrolled into the pilot. Of the first 46 participants released from prison, 42 accepted the first injection of XR-NTX prior to release. Of those, 86% were retained as participants in community (31 still active, and 5 completed 6-month follow-up). Recruitment is planned for a total of 18 months.

**Table 3 Tab3:** Ineligibility for ROAR Pilot Project (First 7 Months Recruitment)

	Number
**Reasons ineligible for pre-screening, post administrative record review (multiple response)**	32
Detainers	14
Mental Health	10
Medical Concerns	6
Refused prior to being presented with information sheet	5
Special Housing	2
Change in Release Date	1
**Reasons Ineligible for Consent/Baseline, post Screening Interview (multiple response)**	79
Does not meet DSM-5 criteria for moderate to severe opioid use disorder	68
Not interested in obtaining treatment to cut back or quit opioid use or to prevent using opioids when released	68
Would not consider medication-based treatment for opioid use disorder	36
Not willing to take at least one evidence-based measure to avoid becoming pregnant	11
Chronic pain that requires ongoing treatment with opioid pain medicine	7
Release outside of target counties	5
Disqualified by prison health services	2
Planning on conceiving in the coming months	1

### Data collection and measures

Our primary outcome is any opioid overdose (fatal or non-fatal) within 6 months following release from incarceration. This is a binary outcome indicating a fatal or non-fatal opioid-related overdose event in the 6 months following release from incarceration. We identify fatal opioid overdose with linked vital statistics data and define fatal overdose using International Classification of Disease, 10th Revision specific codes for opioid poisoning. Non-fatal overdose is measured using Oregon Medicaid and hospitalization discharge data. We use the date of admission as the overdose date. Emergency department encounters occurring within 1 day of a hospitalization are not counted as distinct overdose events. As secondary analyses, we will examine which baseline characteristics are associated with implementation and client outcomes using both descriptive statistics as well as bivariate methods.

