**Methods/design:**

In the week prior to their release, female adults in custody with moderate to severe opioid use disorder start treatment with extended release naltrexone, an injectable opioid antagonist that blocks the effects of opioids for up to 1 month. All ROAR participants receive training to use naloxone rescue kits and are provided nasal naloxone at release. Ongoing support from a certified recovery mentor to facilitate sustained engagement with treatment for substance use disorders begins in the month prior to release from prison and continues for 6 months in community. We evaluate the association between ROAR participation and the primary outcome of opioid overdose.

Using administrative data provided by the Oregon Department of Corrections and the Oregon Health Authority, we compare the odds of overdose among ROAR participants versus a comparison group of females released from prison during the study period. Evaluation activities in community includes survey and qualitative interviews for 6 months post release, as well as a review of clinic records to assess retention on medication among the pilot cohort (*N* = 100).

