Evaluate the effect of the ROAR pilot on opioid overdose among adult women released from prison. We evaluate the association between participation and the primary outcome of opioid overdose, including either a fatal or non-fatal overdose event. Fatal and non-fatal opioid overdoses are assessed for all adult females released from prison during the 18-month study period (expected *n* = 1000) regardless of participation in the ROAR intervention. Using administrative data provided by the Oregon Department of Corrections (e.g., dates of incarceration) and Oregon Health Authority (i.e., Medicaid claims and encounters), we compare the odds of overdose among participants versus a comparison group of previously incarcerated adult females with documented addiction or dependence in administrative records. Data from the comparison group will consist of de-identified administrative data for fatal and non-fatal overdoses in the state. The study will not directly recruit for this group. Statistical analyses adjust for county- and patient-level confounders including level of substance abuse treatment need and mental health treatment need assessed at prison intake.

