#### Informed consent

Those who pass the prescreening and elect to move forward are invited to meet with ROAR study staff for an informed consent and baseline interview no sooner than 90 days prior to release. ROAR participants are consented in a private area within the prison – either in the health services, education or professional visit areas. Only the participant and two study staff will be present. Screening and consent logs are maintained by study staff in REDCap and not shared with prison staff who are not engaged in ROAR.

 Study staff confirm the participant’s eligibility to participate in the pilot intervention prior to meeting and administer a short consent quiz to assess participant’s understanding of the study. If a participant provides an incorrect answer on the quiz, study staff will revisit the necessary information with the participant. Study staff will then re-ask the question, and the participant will write the correct answer on the quiz form.

Potential participants are informed that the participation in the evaluation project is voluntary and that participation will not influence the terms of their release. All inmates with OUD will receive the customary pre-release counseling, regardless of whether or not they decide to participate. At no time during the study will participants be incentivized to accept medical treatment or medication, or to meet with a CRM. Potential participants are notified that survey data will never be shared with corrections or law enforcement officials without their written permission. Participants sign the consent form to enroll in ROAR based on their willingness to receive an injection of XR-NTX and connect with a CRM prior to release to the community, and participate in research activities for up to 24 weeks post release. If a potential participant would like more time to decide to participate or to consult by phone with the study clinician, the research team and prison staff coordinate the necessary meetings to provide information to inform her decision.

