### ROAR intervention

The pre-release phase includes screening and medication initiation activities, which are briefly described below. The post-release phase includes survey and interview data collection and regular participant check-ins, along with community treatment and ongoing support from CRMs. Return to opioid use is an expected part of the recovery process, and all participants are released with nasal naloxone rescue kits. The naloxone kits are reviewed with the participants during the health services visit, at day of release with the CRM, and throughout their follow up in community to assess the need for ongoing education, training, and whether or not the naloxone has been used and there is need for an additional rescue kit. Nasal naloxone is a medication that cannot be abused and has no “street value” in terms of the being sold or traded in community, therefore, there is limited risk of it being sold or stolen. Participants who return to opioid use remain eligible to continue participation in ROAR, to receive support from their CRM, and are contacted for participation in the 3-month and 6-month follow-up interviews. All study procedures and assessments are summarized in Table 2. Note that variation in the timeline is expected, based on changes in participant release dates. If a participant receives an injection of XR-NTX more than 3 weeks prior to release (due to unexpected change in release date), then the participant will be maintained on XR-NTX with monthly injections up to the week prior to actual release.

**Table 2 Tab2:** ROAR Assessments and Study Activities

	Pre-Release ROAR Activities								Release Day	Post-Release ROAR Evaluation Visits						
Tests/ Procedures	Prescreen		Consent & Baseline	CRM Reach In Visits			Health Services			2 Week Check In	1 Month Check In	2 Month Check In	3 Month Follow Up (& Qualitative Interview)	4 Month Check In	5 Month Check In	6 Month Follow Up
**Study Visit Number**	**PS1**	**PS2**	**Consent & Baseline Interview**	**CRM1**	**CRM 2**	**CRM 3** **(optional)**	**HS1**	**HS2**	**V0**	**V1**	**V2**	**V3**	**V4**	**V5**	**V6**	**V7**
**Approximate Weeks Post-Release**	**−12**	**−8**	**−6**	**−4**	**−2**	**−1**	**−4**	**−1**	**0**	**2**	**4**	**8**	**12**	**16**	**20**	**24**
Medical Chart Review	**X**															
Prescreen Interview (DSM-5 OUD)		**X**														
Inclusion/Exclusion Checklist		**X**														
Demographics (Informed Consent and Consent Quiz)			**X**													

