##### CRMs

ROAR’s two partner community treatment programs employ grant-funded female ROAR mentors who are CRMs in the State of Oregon. They meet with ROAR participants during the release planning process and in the community during the 6 months post release while enrolled in the pilot intervention. CRM visits in community are partially reimbursed by state Medicaid, once the participant has enrolled in treatment services at the treatment agency.

A CRM must complete a State of Oregon Behavioral Health Division-approved training program. CRMs are a self-identified person in recovery from a SUD and must meet the abstinence requirements for recovering staff in Oregon’s alcohol and other drug treatment programs (i.e., attestation that CRM has not used alcohol or illicit drugs or abused prescription medication in the two years immediately preceding employment). CRMs in Oregon complete a minimum 40 h of training and undergo a criminal background check and a national psychometric examination in order to obtain state certification. ROAR CRMs have additional training provided by Comagine Health in criminality theory and the role of the forensic peer, gender-specific needs and service delivery, including co-occurring disorders, trauma-informed services, physical health considerations for women, social learning theory, criminality and pro-social behaviors, PREA, and relapse and overdose prevention. CRMs are trained to administer and carry nasal naloxone rescue kits. CRMs are evaluated on the Substance Abuse and Mental Health Services Administration (SAMHSA’s) twelve core competencies for peer workers in behavioral health services throughout the study (SAMHSA, 2015).

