##### Limited Administrative Dataset

Fatal and non-fatal opioid overdoses will be assessed for all women released from prison during the 18 month study period (expected *n* = 1000) regardless of participation in ROAR. Using administrative data provided by the Oregon Department of Corrections and the Oregon Health Authority, study staff will compare odds of overdose among ROAR participants (expected n = 100) versus a comparison group of at least 100 previously incarcerated adult women with a documented SUD who are released into Oregon counties that are not participating in ROAR. Multivariate statistical analyses will be conducted to adjust for county and patient level cofounders including level of substance abuse and mental health treatment needs assessed at intake.

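### The primary outcome counts a non-fatal overdose only if it leaves a Medicaid or hospital record, and ROAR itself can change whether a record is made; the size and net direction of the resulting bias are unknown

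*Protocol article*

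**What the plan says.** All places are in the protocol article.

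- **Outcome.** Data collection and measures: "Our primary outcome is any opioid overdose (fatal or non-fatal) within 6 months following release from incarceration". Deaths come from vital statistics. For the rest, "Non-fatal overdose is measured using Oregon Medicaid and hospitalization discharge data". The Opioid Overdose part of the Analysis section repeats these sources and gives one validity figure for administrative data (sensitivity 97%, specificity 85%), not split by group.
- **ROAR women.** Abstract: "All ROAR participants receive training to use naloxone rescue kits and are provided nasal naloxone at release". The ROAR intervention section has staff review the kits through follow-up, including "whether or not the naloxone has been used and there is need for an additional rescue kit". The CRMs section adds: "CRMs are trained to administer and carry nasal naloxone rescue kits".
- **Features that could raise recording in ROAR.** The naloxone training under CRM reach-in visits covers the law protecting people who seek help for an overdose. SUD treatment in community and CRM support in community describe linkage to Medicaid-covered treatment and frequent mentor contact.
- **Comparison women.** Aim 2: "Data from the comparison group will consist of de-identified administrative data for fatal and non-fatal overdoses in the state". The Limited Administrative Dataset section takes them from women "who are released into Oregon counties that are not participating in ROAR". Their access to naloxone is not described.
- **Self-report.** ROAR women are asked about overdose at 3 and 6 months. The Implementation section reports this as a client outcome within ROAR. It is not used in the between-group analysis.

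**The concern.** The outcome's name covers every opioid overdose; its measurement covers deaths and overdoses that generate a bill or a discharge record. That gap would matter less if it were the same in both groups. Here the intervention includes components that bear on whether an overdose reaches care, so group membership may affect whether an event is seen as well as whether it occurs.

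If more ROAR overdoses are reversed without medical contact, a lower recorded rate could be read as overdoses prevented. If ROAR instead prompts more emergency calls or more contact with covered care, a real benefit could be understated. The covariates and the county random effect act on recorded outcomes and cannot restore unrecorded ones. The limitations in the Discussion name systematic group differences and residual confounding, but not this.

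**Working it through.** **No figure to reproduce.** The document gives no share of overdoses recorded by group, so the calculation below is an illustration under assumptions.

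**Inputs**
- *True risk ratio:* 1.0 (assumed).
- *f, fatal share of overdoses:* 10% (assumed); deaths are taken as always seen. As a rough check, the Background cites 15 non-fatal and 2 fatal overdoses with the same denominator of 283. If these come from one study, the fatal share is 2/17 = 12%.
- *uR and uC:* unseen share of non-fatal overdoses in ROAR and in the comparison group (assumed, varied both ways).
- *From Sample Size and Power:* 100 women per group, baseline 20% to 25% per year.

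**Formula.** Apparent RR = [f + (1 − f)(1 − uR)] / [f + (1 − f)(1 − uC)]

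With f = 0.10 the seen fraction is 1.00, 0.91, 0.82, 0.73 or 0.64 for 0%, 10%, 20%, 30% or 40% unseen. The apparent RR is the ratio of two of these:

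| Unseen, comparison | ROAR 10% | ROAR 20% | ROAR 30% | ROAR 40% |
|---|---|---|---|---|
| 0% | 0.91 | 0.82 | 0.73 | 0.64 |
| 20% | 1.11 | 1.00 | 0.89 | 0.78 |
| 30% | 1.25 | 1.12 | 1.00 | 0.88 |

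Equal capture gives 1.00, and better capture in ROAR gives a value above 1. The first row is the case of an extra loss e in ROAR alone, where RR = 1 − (1 − f)e. It is not sensitive to f: for e = 10%, 20%, 30% it gives 0.90, 0.80, 0.70 at f = 0 and 0.92, 0.84, 0.76 at f = 20%.

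**In numbers of women.** Converting the annual rates to six months under a constant hazard gives 1 − √0.80 = 10.6% and 1 − √0.75 = 13.4%. Among 100 ROAR women, an extra 20% loss removes 10.6 × 0.9 × 0.2 = 1.9 to 13.4 × 0.9 × 0.2 = 2.4 women with an event. A 30% loss removes 2.9 to 3.6.

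**Chance of a false significant benefit.** This uses a simple two-proportion test, two-sided 5%, 100 per group, no clustering; the nominal value in this direction is 2.5%.

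| Extra loss in ROAR | At 20% to 25% risk | At 10.6% to 13.4% risk |
|---|---|---|
| 10% | 5.1% to 5.6% | 4.1% to 4.4% |
| 20% | 9.7% to 11.5% | 6.6% to 7.5% |
| 30% | 17.0% to 21.1% | 10.4% to 12.2% |

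**Scale.** Taking Table 4 as printed, its smallest differences at zero clustering are 0.105 (20% baseline) and 0.12 (25%). For lost recording alone to produce them, e would have to be 0.105/0.20/0.9 = 58% or 0.12/0.25/0.9 = 53%.

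**Per event or per woman.** The formula removes events, but the outcome is defined as yes or no per woman. A woman with two non-fatal overdoses, each unseen with probability 30% independently, is missed with probability 0.3 × 0.3 = 9%. The tables therefore overstate the loss where women have repeated overdoses.

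**The case against.** Four objections have force.

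1. **Comparison women's care.** A reader might infer that they get only counselling and have no naloxone. The Informed consent section does not say that. Its sentence, "All inmates with OUD will receive the customary pre-release counseling, regardless of whether or not they decide to participate", assures inmates that refusal carries no penalty; it does not describe the comparison group's care. Community naloxone in their counties would narrow any gap. What stands is that kits, review and mentors are described for ROAR women and nothing comparable is described for the others.
2. **Direction.** A reader might infer that unseen overdoses fall mainly in ROAR, so the result must favour it. Good Samaritan teaching, mentor contact and linkage to covered care could work the other way, and hospital discharge data partly offset differences in Medicaid enrolment. The net direction is not established.
3. **Hidden events.** A reader might infer that such overdoses disappear from the study. They do not: the Implementation section reports self-reported overdose at 3 and 6 months. They are missing only from the between-group comparison.
4. **Stated validity and candour.** The 97% sensitivity is high, the data sources are openly stated, and the Discussion promises cautious reporting. But the validity figure is a single value, and the article does not say that it covers overdoses that never reached care or that it holds equally in both groups. The promised caution concerns confounding.

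**Conclusion.** The point holds as an unacknowledged limitation of the primary comparison. The outcome is labelled more broadly than it is measured, and the intervention can plausibly alter measurement in one group. Bias in favour of ROAR is plausible but not shown.

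Under the stated assumptions (no true effect, 10% fatal, per-event loss), an extra 10% to 30% of ROAR non-fatal overdoses unseen would move the apparent risk ratio to between 0.91 and 0.73. Equal capture leaves it at 1.0, and better capture in ROAR pushes it above 1. These figures show sensitivity and do not estimate the actual bias. The document supplies no capture rates, and the per-event calculation overstates the effect on a per-woman outcome. The issue deserves correction because it decides what a favourable result may be taken to mean. It does not invalidate the design.

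**What to change.** 1. In Study design, Data collection and measures, and the Opioid Overdose analysis, name the outcome *fatal or medically treated opioid overdose*, and limit the conclusion to that.
2. Report fatal overdose separately, since vital statistics capture it in the same way in both groups. Few deaths are likely, so this will be descriptive.
3. Match ROAR women's self-reported overdoses and recorded naloxone uses to claims and discharge records; participants already authorise linkage to state data under the Inclusion Criteria. Report how many have no record. Separate kits used on the participant from kits used on someone else, and state how many women gave no follow-up survey.
4. Run a per-woman sensitivity analysis over a range of unseen fractions in each group, including equal and reversed capture. Label any analysis that adds unseen events to ROAR alone as a conservative bound, because the comparison women cannot be asked.
5. Add differential ascertainment to the limitations in the Discussion.

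The cost is a narrower headline claim, some wording and one added analysis. No new data collection is needed.

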#### Baseline Surveys and Assessments

During the informed consent/baseline data collection visit with the ROAR staff, participants are asked to complete baseline surveys, which provide individual characteristics that will be used to describe study participants and explore factors potentially associated with implementation and client outcomes. The Baseline Survey collects demographic information, medical status, overdose experiences, psychiatric status and mental health treatment, and PHQ-9 responses. Selected items from the Addiction Severity Index Lite (ASI Lite) will assess an individual’s history related to substance use, family/social status, employment, and medical and psychosocial issues.

*Questionnaires Included in Baseline Survey:*PHQ-9Participant DemographicsASI Lite (selected items)

#### Follow-up Surveys

At 3- and 6-months post-release, participants are invited to complete a 30-minute face to face survey that collects information about medical status, employment/support status, alcohol and drug use, overdose experiences, family/social relationships, psychiatric status and mental health treatment, patient health questionnaire responses, quality of life, criminal justice involvement, treatment services review, and MOUD treatment adherence. The ROAR research coordinator records participant responses directly in REDCap. The survey meetings are conducted in person in a public place of the participant’s choosing.

Items include the ASI-Lite questions adapted for a 3-month timeframe and the overdose experience items. Quality of life is measured using the World Health Organization Quality of Life-8 . Items using previously tested language will capture overdose experience. Participants are compensated 25 USD for completing the 3-month survey and 50 USD for completing the 6-month survey. Information collected from surveys is not shared with law enforcement officials.

